## Aims

The primary aim of this trial is to evaluate the feasibility and effect of a goal-setting health coaching intervention based on initial accelerometer and then pedometer feedback on total sedentary time for 12 weeks compared to one-off advice through a brochure in reducing sedentary behaviour in older people at high risk of falling according to the STEADI criteria (had a fall in last 12 months, feel unsteady when walking or standing, and/or worry about falling) [29].

The secondary aims are to compare the change in sedentary time based on the self-reported Measure of Older Adults' Sedentary Time (MOST) questionnaire [30], FES [31], change in gait speed, proportion of fallers and numbers of falls.

Evaluation of effects at 24 weeks will also occur to determine if the changes seen with the intervention compared to control is sustained at 24 weeks.

It is hypothesized that the intervention will be feasible with a 40% recruitment rate and an 80% retention rate will be achieved at 6 months. For adherence and acceptability, it is hypothesized that goal attainment scale of 0 (indicating goal achieved) for at least three goals will be achieved in 70% of participants (intervention group) and the intervention is acceptable in 70% of the participants. A further hypothesis is that the intervention is effective in reducing sedentary time and the benefits sustained at 24 weeks.

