Domestic—outdoors (e.g., gardening)	Screen-based activities (e.g. computer or tablet)
Transportation	Reading
Recreation	Others

A health coach with medical or nursing background will maintain contact through telephone calls, with participants in the interventional group to monitor progress towards reducing sedentary behaviour and to assist participants to overcome any participation barriers that arise. During the fortnightly telephone contacts, health coaches will also enquire about the circumstance of any falls that participants may have experienced and they will discuss strategies for reducing the risk of future falls. Health coaches will undergo training using written materials prepared by the research team.

A pedometer enhanced with a web-interface, Fitbit Zip™ (San Francisco, CA, USA) will be provided to all intervention group participants to provide feedback on the number of steps achieved daily. These pedometers will be provided as a motivational tool to encourage a reduction in sedentary behaviour. Participants will be encouraged to wear the pedometer during waking hours on a daily basis for the whole 12-week intervention period to record their daily steps and provide feedback and motivation to reduce their sedentary behaviour. Participants will be able to keep the pedometer at the completion of the study.

Participants in the intervention group will also be encouraged to attend falls prevention classes provided through one of the local allied health facilities (http://fallssa.com.au/). The aim of these classes is to help address some of the participants’ risk factors for falls. The participants will pay a small fee to attend these classes. The community aged care service providers will offer these classes. If participants have attended one of these classes in a 12-month period prior to enrolment, they will not be required to repeat these classes. They will be provided with information about what participant should do in the event of a fall (Standing Up to Falls—SA Health).

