Goal attainment scale (GAS) is a method for quantifying progress towards defined goals [39, 40]. Three goals to reduce sedentary behaviour will be established at baseline by participants in the interventional group using the GAS with assistance from the health coach. Another three goals will be determined at the end of week 6. Once the goals are agreed upon, the health coach and participant will then predict the GAS outcomes on a five-point scale ranging from − 2 to + 2, where a score of 0 indicates achievement of the set goal, a score of − 1 indicates no change from the baseline level of ability for that goal type, − 2 indicates worse performance than at baseline and + 1 and + 2 indicate ‘somewhat better’ and ‘much better’ performance than the set goal, respectively. Attainment of the agreed goals to reduce sedentary behaviour will be assessed at both six and 12 weeks after participant randomization by a research assistant who is unaware of group assignment. The motivation for change will be evaluated using the Change Questionnaire [41]. Participants’ motivation will be assessed at T0, T6, T12 and T24.

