### Primary outcomes

#### Feasibility

Feasibility indicators include the trial process (recruitment, retention, acceptability, adherence and safety) in the study. Adherence to the intervention will be assessed according to completion of the goals set and fidelity to phone calls and visits. Acceptability of the intervention will be assessed with a questionnaire.

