### Statistical analyses

Feasibility findings will be primarily descriptive and used as a metric for improvement when compared to similar studies. We hypothesize that the intervention will be feasible among several improvement metrics including 40% or more recruitment rate and less than 20% attrition. This hypothesis is based on findings from earlier studies [13–16].

Descriptive analyses will be conducted using mean with standard deviation, median with interquartile range and frequency for baseline characteristics. These characteristics include age, gender, ethnicity, physical function, health status, quality of life and mental status. Mean group differences will be examined using independent samples *t* test for normally distributed data and nonparametric tests (Kruskal-Wallis and Mann-Whitney *U*) for non-normally distributed data. Differences in frequency of variables will be compared using chi-square test.

Analysis of variance (ANOVA) will be used to test the post-intervention difference at 12 and 24 weeks between the two groups. The covariates in the analysis will include baseline values of the dependent variable and any variable significantly different between groups at baseline. Group mean values for adherence variable at 12 and 24 weeks (retention rate, days the accelerometer and pedometer are worn) will be analysed by an independent *t* test. The data analysed will be based on the intention-to-treat analysis.

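### Pedometer wear is sent to a between-arm t test although only the intervention arm has a pedometer, and the goal-attainment criterion should say a score of 0 or higher

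*Protocol article*

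**What the plan says.** **The test.** Statistical analyses in the protocol article lists the adherence variables as "Group mean values for adherence variable at 12 and 24 weeks (retention rate, days the accelerometer and pedometer are worn") and says that they "will be analysed by an independent" t test. The same section has a separate rule for categorical data: "Differences in frequency of variables will be compared using chi-square test".

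**Who has a pedometer.** Under Intervention group, the device "will be provided to all intervention group participants to provide feedback on the number of steps achieved daily". These participants are encouraged to "wear the pedometer during waking hours on a daily basis for the whole 12-week intervention period", and they keep the device when the study ends. Under Control group, the only thing that controls receive beyond usual care is their first accelerometer result. Table 1 lists a pedometer among the materials without naming an arm. Table 4 schedules step counts and pedometer adherence at weeks 6, 12 and 24.

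**The goal criterion.** The Aims expect that a "goal attainment scale of 0 (indicating goal achieved) for at least three goals will be achieved in 70% of participants (intervention group"). The scale, defined under Intervention group, runs from −2 to +2: "a score of 0 indicates achievement of the set goal", and +1 and +2 mean that the participant did better than the goal. Each participant sets six goals, three at baseline and three at week 6.

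**Place in the plan.** Feasibility is a primary outcome. Under that heading, "Adherence to the intervention will be assessed according to completion of the goals set and fidelity to phone calls and visits".

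**The concern.** An independent t test needs observations in two groups. For pedometer days the control group has none, so the prescribed analysis either cannot be run or is run on zeros that follow from the design. The second case is the worse one: it produces a small p-value that could be reported as better adherence in the intervention arm when it shows only which arm was handed the device.

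The goal criterion is a numerical target for a primary outcome. If an analyst applies its wording literally, a participant who exceeds every goal fails, and the 70% target can be missed because participants did too well.

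Retention is one yes or no per participant. Sending it to a t test sits oddly beside the chi-square rule in the same section.

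**Working it through.** **1. Pedometer days**

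The plan's own figure first: 64 evaluable participants and 20% attrition give 64 / (1 − 0.20) = 80. This matches Power calculation and is not in dispute. It gives 32 evaluable participants per arm.

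- *Control values missing:* there is no second group, and the t test returns no value.
- *Control values set to 0:* the documents give no SD for pedometer days, so assume 20 days in the intervention arm. The control SD is 0.
  - Pooled SD = √((20² + 0²)/2) = 14.14.
  - t = mean / (14.14 × √(2/32)) = mean / 3.536, on 62 degrees of freedom.

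| Mean days, intervention arm | t | p |
|---|---|---|
| 5 | 1.41 | 0.16 |
| 10 | 2.83 | 0.006 |
| 20 | 5.66 | 4 × 10⁻⁷ |

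Twelve weeks of daily wear is 84 days. A mean of 10 days would be poor adherence, yet the test would call it a clear difference in favour of the intervention arm.

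Accelerometer days are different. Both arms wear that device at baseline and at weeks 12 and 24, so a between-arm comparison is possible.

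**2. Goal criterion**

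Assume six independent goals, each with probability a of scoring 0 or higher, and let a share s of those achieved goals score +1 or +2. The documents give neither a nor s, nor do they support independence.

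- Reading "0 or higher": P(at least 3 of 6) with probability a per goal.
- Reading "exactly 0": P(at least 3 of 6) with probability a(1 − s) per goal.
- P(at least 3 of 6) = 1 − [(1 − p)⁶ + 6p(1 − p)⁵ + 15p²(1 − p)⁴].

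Example, p = 0.60 × 0.70 = 0.42: 1 − (0.038 + 0.165 + 0.299) = 0.497.

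| a | s | p if exactly 0 | Meets "0 or higher" | Meets "exactly 0" |
|---|---|---|---|---|
| 0.60 | 20% | 0.48 | 82% | 62% |
| 0.60 | 30% | 0.42 | 82% | 50% |
| 0.70 | 20% | 0.56 | 93% | 76% |
| 0.70 | 29% (20 of 70 points) | 0.50 | 93% | 66% |
| 0.70 | 43% (30 of 70 points) | 0.40 | 93% | 46% |

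The literal reading crosses 70% between p = 0.52 (69.3%) and p = 0.53 (71.1%). The two readings therefore give opposite answers in some plausible cases and the same answer in others.

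**3. Retention**

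Compare a t test on 0/1 data with the uncorrected chi-square test at 40 per arm.

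| Retained, of 40 vs 40 | t test p | Chi-square p |
|---|---|---|
| 32 vs 36 | 0.215 | 0.210 |
| 29 vs 36 | 0.046 | 0.045 |
| 28 vs 36 | 0.025 | 0.025 |

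For the first row, chi-square = 80 × (32×4 − 36×8)² / (40 × 40 × 68 × 12) = 1.57. Exact enumeration gives the same type I error for both tests (0.051 at 80% retention, 0.059 at 90%), and the decisions at the 0.05 level agree.

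**The case against.** **Reach of the pedometer slip.** No numerical target uses pedometer days, and the Feasibility section measures adherence by goals, calls and visits. With control data missing, the test would fail visibly. This limits the damage, but it does not rescue the sentence, and the version with zeros would not fail visibly. Table 1's unassigned pedometer does not help either, because the specific text on the two arms settles who receives one.

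**Week 24.** A reader might infer that measuring pedometer wear at week 24 is itself an error, because wear is requested for 12 weeks only. The documents do not support this. Table 4 schedules the measurement and participants keep the device. It needs to be reported separately, not dropped.

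**Goal criterion.** A reader might infer that the plan counts only scores of exactly 0. Nowhere does it say only or exactly, and the gloss in the Aims explains 0 as the goal having been achieved. A goal that is beaten is also achieved, so 0 or higher is very probably what was meant. That stands, and it makes this a correction of one phrase. The sizes shown rest on assumed inputs, and the row at 76% shows that the literal reading need not miss the target.

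**Retention.** A reader might infer that the t test gives wrong results. At this sample size it does not; the check above shows the same decisions as chi-square.

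**Retention boundary.** The Aims speak of 80% retention and Statistical analyses of attrition below 20%. These differ only at exactly 64 of 80 retained, and no decision is tied to that boundary.

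**Conclusion.** The pedometer part holds without assumptions about data: the prescribed two-arm comparison has no control observations, or has zeros created by the design. The p-values for the zero case are illustrations that rest on an assumed SD of 20 days and 32 per arm.

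The goal criterion holds as a wording fault. Its literal form can move the result from 82% to 50%, or leave it above target at about 76%, depending on success rates, overshoot and independence that the documents do not give.

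The retention test is a matter of consistency with no effect on decisions.

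A reader might infer that these figures decide whether a larger trial goes ahead. The article sets no progression rule: it presents the targets as hypotheses, calls the feasibility findings primarily descriptive, and in the Discussion looks ahead only to improving later coaching programmes. What is at stake is a correct report of feasibility.

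**What to change.** - **Pedometer days:** remove them from the two-arm test. Summarise them in the intervention arm only, with the 12-week wear period reported separately from the week-24 measurement in Table 4.
- **Accelerometer days:** keep the between-arm comparison.
- **Goal criterion in the Aims:** change the score of 0 to a score of 0 or higher on at least three goals.
- **Retention:** report proportions per arm, in line with the chi-square rule already in Statistical analyses.

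The cost is wording only. No data collection, visit or sample size changes.

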### Power calculation

Sixty-four participants will be required to detect a 30 min/day reduction [15] in sedentary time (80% power, alpha 0.05) in the interventional group, assuming there is no change in the control arm. Therefore, the aim is to recruit 80 participants (40 in each arm) to allow for 20% attrition. The same number of male and female participants will be recruited.

## Discussion

This study is highly important because of the dual significance of falls and sedentary behaviour among older people. This trial is the first to integrate strategies using feedback from accelerometer and goal-setting health coaching in older people who have had a fall in the last 12 months or are at risk of falling.

Currently, there is limited work on community-based interventions to reduce sedentary behaviour in older people that can alter the risk of falls. This trial will address a key gap in the current evidence regarding effective ways to reduce sedentary behaviour in older people and the use of an accelerometer as a tool to motivate change in behaviour. It will provide a model for integrated falls and sedentary behaviour assessment and reduction programme that could be implemented in community health care settings. If such intervention with health coaching on sedentary behaviour is effective in reducing falls, it has enormous potential benefit for older people and the health care system. The trial findings will be disseminated in peer-reviewed journals and through scientific and professional conferences. The target in step count of an average of 200 steps per week increment was adopted for this study because it was seen as a realistic increase to achieve in 1 week. One previous study has used 1500 steps over 4 weeks which would be an average of 375 steps/week increment [57]. This has been revised to a lower target given that our participants are at risk of falls and may require a more gradual increment. Since no evidence exists to guide goals for sedentary time, behaviour change researchers suggested a 30-min improvement in sedentary time would be realistic for participants to achieve during the 12-week intervention [13, 57].

One of the limitations of the study is that the research personnel performing the assessment may not be fully blinded to the group participants that are allocated into because participants may inadvertently reveal this information. In addition, this is a small study and is not adequately powered to evaluate the effects of this intervention on the rate of falls. The duration of the study is also relatively short. Therefore, the sustainability of any behaviour changes beyond the study period is uncertain. Information about any falls in the control group is collected over a 6-week period which can lead to inaccurate recall from participants. However, it serves as a useful pilot study that can be used to enhance future health coaching programs on reducing sedentary behaviour among older people at risk of falls.

## Abbreviations

ADLs: Activities of daily living
ANOVA: Analysis of variance
ASM: Appendicular skeletal muscle mass
BIA: Bioelectrical impedance analysis
BMI: Body mass index
CCI: Charlson comorbidity index
CONSORT: CONsolidated Standards of Reporting Trials
EQ5D: European Quality of Life
FES: Falls efficacy scale
GAS: Goal Attainment Scale
IPAQ: International Physical Activity Questionnaire
MOST: Measure of Older Adults' Sedentary Time
MVPA: Moderate to vigorous physical activity
NEWS: Neighbourhood Environment Walkability Scale
SDT: Self-determination theory
SMART: Specific, Measurable, Attainable, Realistic, Time-bound
SPIRIT: Standard Protocol Items: Recommendations for Interventional Trial
SPPB: Short physical performance battery
TIDieR: Template for Intervention Description and Replication
